# A randomized, multi-center, open-label study to compare the safety and efficacy between afatinib monotherapy and combination therapy of afatinib and HAD-B1 for the locally advanced or metastatic NSCLC patients with EGFR mutations

**DOI:** 10.1097/MD.0000000000023455

**Published:** 2020-12-04

**Keywords:** afatinib, HAD-B1, herbal medicine, non-small cell lung cancer, randomized controlled trial

## Abstract

**Background::**

Afatinib is an epidermal growth factor receptor - tyrosine kinase inhibitor (EGFR-TKI) with proven efficacy for treating patients with advanced or metastatic non-small cell lung cancer (NSCLC). Unfortunately, responses are limited by acquired resistance. Because traditional Korean medicine may have synergistic effects when combined with chemotherapy or radiotherapy, the aim of our study is to elucidate the efficacy and safety of afatinib plus HangAmDan-B1 (HAD-B1) combination therapy in the treatment of patients with NSCLC, as well as EGFR mutations, who need afatinib therapy.

**Methods/design::**

This study is a randomized, multi-center, open clinical trial. A total of 142 eligible subjects, recruited at 8 centers, are randomly assigned to take Afatinib (20–40 mg) ± HAD-B1 (0.972 g/day) for 16 weeks. In the test group, HAD-B1 and afatinib will be used in combination. The primary outcome is a comparison of starting dose maintenance rate as well as the disease control rate (DCR) between afatinib monotherapy and afatinib plus HAD-B1 combination therapy in patients with local advanced or metastatic (Stage IIIA, B, C/IV) NSCLC. Secondary outcomes are the Progression Free Survival (PFS), Time to progression (TTP), Overall survival rate, ORR based on RESIST 1.1, tumor size reduction, health-related quality of life (HRQoL), and Tumor marker.

**Discussion::**

The result of this clinical trial will provide evidence for the efficacy and safety of using HAD-B1 in the treatment of EGFR-positive patients with locally advanced or metastatic NSCLC who require afatinib therapy.

**Trial registration::**

Clinical Research Information Service (CRIS), Republic of Korea (ID: KCT0005414), on September 23, 2020.

## Introduction

1

Around 85% of primary lung cancers are non-small cell lung cancer (NSCLC).^[1]^ Numerous oncogenic drivers, including mutations in the genes encoding the epidermal growth factor receptor (EGFR), have been recognized in NSCLC. EGFR mutations are found in 47% of lung adenocarcinomas, the most frequent NSCLC subtype in Asia-Pacific, and in 43% of the adenocarcinomas in the Republic of Korea.^[2]^ The activating mutations in EGFR lead to increased signaling downstream of the receptor, resulting in cellular growth and proliferation and in the promotion of tumor development due to enhanced metastatic spread and resisting apoptotic signals.^[3]^ Platinum-based chemotherapy has been the basis for the treatment of patients with advanced or metastatic NSCLC, but the availability and use of EFGR - tyrosine kinase inhibitors (EGFR TKIs) have significantly changed the management of patients with NSCLC harboring EGFR mutations. Gefitinib, erlotinib, and afatinib are 3 widely used EGFR-TKIs with proven efficacy for the treatment of patients advanced or metastatic NSCLC.^[4]^

In 2013, afatinib was approved by the U.S. FDA for the first line treatment of patients with locally advanced or metastatic NSCLC who harbor nonresistant EGFR mutations.^[5]^ The clinical effectiveness of afatinib in the treatment of such patients has been confirmed by the results of recent real-world studies.^[6]^ Despite the high disease control rates, almost all patients eventually experience acquired resistance-mediated disease progression. Therefore, new combination regimens are needed to delay or overcome this acquired TKI resistance.

HangAmDan-B1 (HAD-B1) is a traditional Korean medicine composed of *Panax ginseng C.A., Panax notoginseng Radix, Cordyceps militaris, and Boswellia carterii BIRDWOOD* (Table 1). Preclinical studies have shown that HAD-B1 has an anti-lung-cancer effect in xenograft animal model experiments using A549 lung cancer cells and A549/CR cells.^[7]^ The results revealed that the activities of caspase-3, -8, and -9 in the HAD-B1-treated group were generally increased in the same way as they were in the afatinib group, suggesting its potential as a novel therapeutic agent for use in afatinib plus HAD-B1 combined therapy for inhibiting acquired resistance. Also, our previous exploratory study to assess the efficacy and safety of HAD-B1 for dose-finding in EGFR-positive NSCLC subjects who need afatinib therapy is currently in progress.^[8]^

**Table 1 T1:** Components of HAD-B1.

Scientific name	Plant parts used	Representative component	Amount (mg)
Panax Notoginseng (Burk) F.H. Chen	Root	Notoginsenoside R1	839
Cordyceps militaris	Fruit and corpus	Cordycepin	640
Panax ginseng C.A. Meyer	Root	Ginsenoside Rg1 and Rb1	640
Boswellia carterii BIRDWOOD	Mastic	a-boswellic acid, b-boswellic acid	400

The aim of this study is to use a multicenter, randomized, controlled trial to explore the efficacy and safety of combination therapy with afatinib plus HAD-B1 in the treatment of patients with locally advanced or metastatic NSCLC who have an activating EGFR mutation. Moreover a cold-heat pattern identification questionnaire (CHPIQ) of NSCLC patients will be conducted to explore whether the prognosis varies according to cold-heat pattern in Korean medicine.

## Methods

2

### Trial design

2.1

This clinical trial is a randomized, multi-centre, open-label study that aims to compare the safety and efficacy between afatinib monotherapy and combination therapy with afatinib plus HAD-B1 for the treatment of patients with locally advanced or metastatic EGFR-mutation-positive NSCLC. Participants will be randomized using a ratio of 1:1 into a treatment group (afatinib 20–40 mg/day plus HAD-B1 2 tablets [972 mg/day]) and a control group (afatinib 20–40 mg/day monotherapy) and will be treated for 16 weeks. As treatment continues, follow-up visits will be scheduled at Day 1, week 2, 4, 8, and 16. Physical examination, vital signs, ECOGPS, clinical laboratory examination, tumor marker examination, imaging diagnosis and tumor evaluation, health-related quality of life survey, combined drug confirmation, and abnormal case evaluation are all performed during each visit. Furthermore, for cold-heat pattern identification and genetic search studies, PMRA chip tests and cold-heat pattern identification surveys are performed prior to randomization.

### Recruitment and consent

2.2

A total of 142 EGFR-mutation-positive patients with locally advanced or metastatic NSCLC patients who need afatinib therapy will be recruited at 8 centers. All subjects will undergo standardized interviews and receive clinical research information on the trial. Written informed consent will be obtained from each subject. The purpose, procedure, and potential benefits and risks of the study will be thoroughly explained to the subjects. The subjects can withdraw from the study at any time without consequence. The trial covers the period from October 31, 2020 to December 2, 2022 (anticipated), including the enrollment and follow-up periods (Fig. 1).

**Figure 1 F1:**
[figure not shown]
Study flow chart.

### Inclusion criteria

2.3

Participants meeting the following criteria will be included:

1.Pathologically confirmed locally advanced or metastatic NSCLC (Stage IIIA-IV based on the eighth edition of the American Joint Commission on Cancer TNM staging system)^[9]^;2.Mutated EGFR and requiring first line afatinib therapy (in the judgment of the researcher);3.Disease measurable using Response Criteria for Clinical Trials of Cancer (RECIST) 1.1^[10]^;4.ECOG performance status score from 0 to 2^[11]^;5.Ability to take the drug orally (in the judgment of the researcher);6.Nineteen years of age or older;7.Willingness to sign a written consent to participate in this trial.

### Exclusion criteria

2.4

Participants who meet 1 or more of the following criteria will be excluded:

1.Presence of a mutated T790M (threonine-to-methionine amino acid change at position 790) of the EGFR kinase domain (acquired, rebiopsy);2.Presence of an active brain metastasis that has been stable for <4 weeks and with symptoms or leptomeningopathy; nevertheless, patients undergoing dexamethasone treatment may be allowed if a stable dose can be administered for at least 4 weeks;3.Presence of gastrointestinal disorder with diarrhea, which is severe or unregulated within 2 weeks after screening, as a major symptom; for example, Crohn disease, absorption disorder, or pathological diarrhea with common terminology criteria (CTC) grade 2 or higher (by assessment of the researcher);4.Presence of interstitial lung disease assessed as unsuitable for this trial by the researcher;5.Severe hepatopathy (Child Pugh C);6.Severe nephropathy (eGFR <15 ml/minute) or the need for dialysis;7.Clinically significant cardiovascular disease (New York Heart Association (NYHA) class 3 congestive heart failure, unstable angina or uncontrolled arrhythmia, myocardial infarction, angina within 1 year of study participation, etc.);8.Fertile women who do not use proper contraception prior to the start of this clinical trial;9.Lactating women or pregnant women;10.Suspicion of having or having been diagnosed with serious mental illness, such as drug abuse, alcoholism, etc;11.Hypersensitivity to afatinib or other EGFR medications;12.Hypersensitivity to HAD-B1 or its constituents;13.Participation in any other clinical trials within the previous month before the;14.Unsuitability for this clinical trial, as determined by the researcher, including severe infectious disease or organ failure.

### Interventions

2.5

Patients in the treatment group will receive of 1 capsule/day of afatinib (20–40 mg/day orally) plus 2 HAD-B1 tablets (972 mg/day, bid orally) while those in the control group will only receive 1 capsule/day of afatinib (20–40 mg/day orally), which may be changed based on the medical judgment of the investigator. The investigator may extend the duration of the drug’s administration. The HAD-B1 tablets used in this trial will be purchased from the Hanpoong Pharmaceutical Co., Ltd. (Seoul, Korea). HAD-B1 is a medical substance containing *Panax ginseng C.A.* (640 mg), *Panax notoginseng Radix* (839 mg), *Cordyceps militaris* (640 mg), and *Boswellia carterii BIRDWOOD* (480 mg) as raw material medicines. In the toxicity assessment of HAD-B1 orally administered to rats for 13 consecutive weeks, the no-observed-adverse-effect-level (NOAEL) for HAD-B1 was determined as 2000 mg/kg/day. The human equivalent dose (HED) was calculated as approximately 320 mg/kg/day, which was about 19 g/day for a person of 60 kg.^[12]^ The dose of HAD-B1 in this clinical trial is approximately 1/20 of that. In the treatment group, when afatinib is removed, HAD-B1 is also removed; however, when afatinib is reduced, HAD-B1 is not reduced.

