### Outcome measures

2.6

**The primary measurement** is comparison of starting dose maintenance rate for afatinib and disease adjustment rate (DCR) at 16 weeks in accordance with RECIST 1.1 of Afatinib + HAD-B1 combined group and afatinib monotherapy group. The secondary outcomes are comparisons of the Progressive Free Survival (PFS) determined by RESIST 1.1, overall survival rate (OS), objective response rate (ORR), tumor size reduction, time to progression (TTP), HRQoL, and tumor markers (CEA, NSE) between the 2 groups. The PFS, ORR, DCR, and TTP are evaluated on the basis of RECIST 1.1 criteria.^[10]^ This clinical trial will explore whether the prognosis varies according to cold-heat pattern in Korean medicine. Cold-heat pattern identification will be evaluated using the usual symptom-based CHPIQ, which has been recognized for its reliability and validity.^[13]^

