### Randomization and blinding

2.8

Random assignment will be performed using a computer-generated, blocked, random-allocation sequence with a 1:1 ratio. Each participant will be assigned to a group according to a pre-generated randomization table and an assigned randomized number. Each participant will be assigned to a treatment group, or the control group according to the allocation codes of the randomized assignment method, which will be prepared in advance. In this clinical trial, blinding is not performed.

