### Sample size calculation

2.9

According to the paper, the Afatinib group’s starting dose maintenance rate is assumed to be 57.6 percent, while the Afatinib + HAD B1 group’s starting dose maintenance rate is assumed to be 80.0 percent. Furthermore, it is assumed that all patients will be recruited and monitored for at least 16 weeks. As a result, each group has 64 test subjects. With a 10% dropout rate, 71 people will be recruited for a total of 142 people.^[14]^

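### The endpoint that sizes the trial is keeping a starting dose that may lie anywhere in 20–40 mg, yet the stated test ignores that dose and the article does not say it is fixed before open allocation

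*Protocol article*

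**What the plan says.** Section 2.6 (Outcome measures) of the protocol article gives the primary measurement as "comparison of starting dose maintenance rate for afatinib and disease adjustment rate (DCR) at 16 weeks". The sample size in section 2.9 rests on the first of these alone: "the Afatinib group’s starting dose maintenance rate is assumed to be 57.6 percent" and "the Afatinib + HAD B1 group’s starting dose maintenance rate is assumed to be 80.0 percent", leading to 64 per group, or 71 per group with 10% dropout.

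Afatinib is given as a range in both arms. Section 2.1 (Trial design) describes "a control group (afatinib 20–40 mg/day monotherapy" and uses the same range for the combination arm. Section 2.5 (Interventions) repeats the range and adds that the treatment is one "which may be changed based on the medical judgment of the investigator".

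On allocation, section 2.8 says: "Random assignment will be performed using a computer-generated, blocked, random-allocation sequence with a 1:1 ratio". It names no stratification factor. It also says: "In this clinical trial, blinding is not performed".

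Section 2.10.1 compares the groups on both primary endpoints with a chi-square or Fisher test. It mentions no adjustment.

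**The concern.** Success is defined relative to each patient's own starting dose. If patients start at different doses within the range, their chance of success probably differs for reasons unrelated to HAD-B1. Someone at the bottom of the stated range has no lower step inside it; someone at the top does. The arm-level maintenance rate is then a weighted average over starting doses, and the weights matter.

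In a blinded trial, or one where the starting dose is settled before allocation, randomisation balances those weights apart from chance. Here allocation is open, and the article does not say when the starting dose is settled. If it can be settled once the arm is known, the mix can differ systematically between arms, and the stated test cannot separate that from a treatment effect.

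A second issue runs alongside. The event that ends maintenance is a dose change or a stop. Section 2.5 leaves dose changes to the judgment of investigators, who know the arm.

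**Working it through.** **Reproducing the plan's own figure.** Inputs from section 2.9: 57.6% vs 80.0%. Alpha and power are not given there; I assume two-sided 5% and 80%.

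n = (0.576×0.424 + 0.80×0.20) × (1.960 + 0.842)² / 0.224² = 63.2, rounded up to 64 per group.

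This matches the plan. An exact enumeration of the chi-square test at 64 per arm gives 79.5% power at the planned rates and 5.2% rejection when both arms are at 57.6%. The sample size arithmetic is not at fault.

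**Bias from an unequal dose mix.** Let q be the share of an arm starting at 20 mg, m_low their maintenance rate, and m_high the rate in the rest.

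- Arm rate = (1 − q)×m_high + q×m_low.
- With no HAD-B1 effect, the spurious difference = (q_test − q_control) × (m_low − m_high).

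The documents give neither the dose mix nor dose-specific rates, so these are assumptions: q = 10% in control and 30% in test, m_high = 57.6%, m_low from 75% to 95%. Rejection rates are exact, two-sided 5% chi-square, 64 per arm.

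| m_low | Control | Test | Spurious difference | False positives |
|---|---|---|---|---|
| 75% | 59.3% | 62.8% | 3.5 points | 7.4% |
| 85% | 60.3% | 65.8% | 5.5 points | 10.4% |
| 95% | 61.3% | 68.8% | 7.5 points | 14.8% |

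For the last row: 0.9×0.576 + 0.1×0.95 = 0.613, and 0.7×0.576 + 0.3×0.95 = 0.688.

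**What stratifying does.** Simulation of 100,000 trials, 64 per arm, no treatment effect, assumed maintenance of 50% at the higher and 80% at the lower dose:

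| Lower-dose share, control vs test | Spurious difference | Unadjusted error | Mantel-Haenszel error |
|---|---|---|---|
| 50% vs 50% | 0 points | 5.2% | 5.0% |
| 40% vs 60% | 6 points | 11.3% | 4.9% |
| 30% vs 70% | 12 points | 30.3% | 5.1% |

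**Hiding an effect.** Take assumed control rates of 50% and 75% and a true gain of 22.4 points at each dose. Power is 79.3% when 30% of each arm start low. It is 59.3% unadjusted when 50% of control and 30% of test start low; the stratified test keeps 81.6%.

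These simulations assume that patients at a given starting dose are comparable between arms. That is secured when the dose is fixed before allocation, but not when it is chosen afterwards.

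**If the dose is fixed before allocation.** With half of each arm starting low, the difference in share has standard deviation √(2×0.5×0.5/64) = 0.088, so a 95% range of about ±17 points. Multiplied by a gap in maintenance of 22.4 to 40 points, that moves the observed difference by about 4 to 7 points in an unlucky trial. Over repeated trials the unadjusted test keeps its error at 5.1–5.2%.

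**The case against.** The strongest reply is that the article does not establish the damaging scenario. Much of this stands.

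- **Who picks the starting dose, and when.** A reader might infer that the unblinded investigator picks it after seeing the arm. The sentence in section 2.5 concerns changing treatment, not choosing the starting dose, and no section says when that dose is set. Systematic bias is a possibility left open, not a stated feature.
- **What the range means.** The 20–40 mg range could include later reductions, which section 2.5 itself discusses. If all patients started at one dose, there would be no mix to worry about.
- **Stratification.** A reader might infer that there is none. That rests on silence in a condensed article; the full protocol may name factors. The unadjusted test is different, because section 2.10.1 states it.
- **Failure at the bottom of the range.** One might say a 20 mg starter can fail only by stopping. The text allows the dose to be changed, not only reduced, and does not exclude counting an increase as loss of the starting dose. The 95% rate is therefore only the top of an assumed range.
- **Loss of power.** A reader might conclude that 30% of patients starting at 20 mg in both arms cuts power to 56%. That takes 95% maintenance at 20 mg and no HAD-B1 benefit there. With 80% maintenance at 20 mg, power is 52% with no benefit in those patients, or 83% with the same 22.4-point gain (capped at 100%). It also assigns 57.6% only to patients above 20 mg, although section 2.9 gives it for the whole afatinib group. No loss of power can be claimed.
- **Withheld reductions.** If one in five control-type failures were withheld in the test arm, the rate would be 0.576 + 0.2×0.424 = 66.1%, and an inert product would reach significance 17.5% of the time. That treats every failure as a discretionary reduction and none as a discontinuation, so it overstates the size.

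What remains is stated text: an endpoint relative to a starting dose, a dose range, open allocation, investigator judgment over changes, and an unadjusted test.

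**Conclusion.** The point holds in conditional form. The stated analysis offers no protection if the starting-dose mix differs between arms, and the article gives no assurance that the starting dose is settled before allocation is known.

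If it is not, a 20-point difference in the share starting at 20 mg would produce 3.5–7.5 points of bias and 7–15% false positives on the assumptions shown, and larger differences would do more. Matching the whole planned 22.4-point effect would take an extreme mix, for example a 56-point gap in share with a 40-point gap in maintenance (0.56×0.40 = 0.224).

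If the dose is settled beforehand, type I error is sound, and stratifying offers only protection against chance imbalance and some precision.

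Every dose-specific rate and every dose mix here is assumed; none comes from the article. Calling this endpoint the main one is also an inference from the sample size, since disease control is listed beside it. Investigator discretion over dose changes in an open trial is a real but unquantified risk to the same endpoint.

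**What to change.** 1. Require the intended starting dose to be entered in the EDC before the allocation is released.
2. Replace the unadjusted primary test of dose maintenance in section 2.10.1 with a Cochran-Mantel-Haenszel test and a common risk difference, stratified by that pre-allocation dose. If enrolment has not begun, stratify the blocked randomisation list by it as well.
3. For any patients whose starting dose was chosen after allocation, treat the stratified result as a sensitivity analysis only. The dose is then a post-randomisation variable, and stratifying on it does not restore a randomised comparison.
4. Record the reason and grade for every dose change in the e-CRF. Section 2.7 records reasons only for discontinuation. Add a sensitivity analysis counting only changes with a documented adverse event.

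The cost is one extra EDC field before randomisation, the reason and grade items for dose changes, a slightly more complex randomisation list and some analysis wording. The sample size stays as it is, and no dose or dose rule changes.

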### Outcome measures

2.6

**The primary measurement** is comparison of starting dose maintenance rate for afatinib and disease adjustment rate (DCR) at 16 weeks in accordance with RECIST 1.1 of Afatinib + HAD-B1 combined group and afatinib monotherapy group. The secondary outcomes are comparisons of the Progressive Free Survival (PFS) determined by RESIST 1.1, overall survival rate (OS), objective response rate (ORR), tumor size reduction, time to progression (TTP), HRQoL, and tumor markers (CEA, NSE) between the 2 groups. The PFS, ORR, DCR, and TTP are evaluated on the basis of RECIST 1.1 criteria.^[10]^ This clinical trial will explore whether the prognosis varies according to cold-heat pattern in Korean medicine. Cold-heat pattern identification will be evaluated using the usual symptom-based CHPIQ, which has been recognized for its reliability and validity.^[13]^

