#### Analysis of first outcome variables

2.10.1

The frequency and percentage of afatinib’s initial dose maintenance rate for afatinib and disease control rate (DCR) according to RECIST 1.1 up to 16 weeks relative to baseline will be presented, and the statistical significance of differences between groups will be analyzed using Chi-square test or Fisher’s effect test.

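### Two primary endpoints are each tested without a stated success rule, and the sample size was derived from only one of them

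*Protocol article*

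**What the plan says.** Section 2.6 defines the primary measurement as the "comparison of starting dose maintenance rate for afatinib and disease adjustment rate (DCR) at 16 weeks in accordance with RECIST 1.1", compared between the two arms. The abstract (Methods/design) names the same pair: "starting dose maintenance rate as well as the disease control rate (DCR").

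Section 2.10.1 treats the two alike. Both are summarised by counts and percentages over the 16 weeks, and one sentence on testing serves for both: "statistical significance of differences between groups will be analyzed using Chi-square test", with a Fisher test as the alternative. It gives no order of testing, no division of the significance level, and no statement of which results would make the trial positive.

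Section 2.9 works with one endpoint. The afatinib group's "starting dose maintenance rate is assumed to be 57.6 percent" and the combination group's "starting dose maintenance rate is assumed to be 80.0 percent". From these, "each group has 64 test subjects", raised to 71 per group (142 in total) for 10% dropout. No DCR figure enters, and the significance level, sidedness and power are not printed.

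**The concern.** The endpoints, the tests and the sample size are all stated, but they do not fit together. With two primary endpoints, the success rule determines both the error rate and what the sample size has to cover.

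- If a win on either endpoint is enough, two full-level tests give the trial two chances of a false positive.
- If both must be won, the 64 per group was calculated for only one part of the success criterion.

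With neither rule fixed, a trial that wins on one endpoint and fails on the other could be called positive or negative after the results are seen. An analysis plan written later can settle the error control, but it cannot by itself make 142 patients adequate for an endpoint that was never sized.

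**Working it through.** **Inputs.** From section 2.9: rates of 0.576 and 0.800 for dose maintenance, and 64 evaluable patients per group. From section 2.1: 1:1 allocation. Assumed, because not printed: two-sided 5% significance and 80% power. Also assumed: all DCR rates and the correlation between the two endpoints.

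**1. Reproducing the 64.** The unpooled normal formula is

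n = (1.960 + 0.842)² × [p₁(1 − p₁) + p₂(1 − p₂)] / (p₂ − p₁)²

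= 7.849 × (0.2442 + 0.1600) / 0.224² = 7.849 × 0.4042 / 0.0502 = 63.2, rounded up to 64.

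The pooled formula gives 66. A one-sided 5% test at 80% power gives 50 to 52 without continuity correction, and two-sided 5% at 90% power gives 85 to 88. So two-sided 5% with 80% power is the natural reading, and dose maintenance alone accounts for the whole sample size. Power at 64 per group is 78.8% by the pooled normal approximation and 79.5% by exact enumeration of the chi-square test.

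**2. If either endpoint suffices, each at two-sided 5%.** For independent tests the family-wise error is 1 − 0.95² = 9.75%. For correlated tests it comes from the bivariate normal distribution. The last column counts only false results in favour of HAD-B1. For independent tests that is 1 − 0.975² = 4.9%, against 2.5% for a single test.

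| Correlation | Any false positive | Falsely favouring HAD-B1 |
|---|---|---|
| 0 | 9.75% | 4.9% |
| 0.5 | 9.1% | 4.5% |
| 0.7 | 8.3% | 4.2% |
| 0.9 | 7.0% | 3.5% |

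**3. If both are required.** Type I error needs no adjustment. Joint power cannot exceed the power for dose maintenance, about 79%. Exact chi-square power for DCR at 64 per group, multiplied by 0.795 (independence), gives:

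| Assumed DCR, control vs combination | DCR power | Joint power |
|---|---|---|
| 85% vs 90% | 13% | 10% |
| 90% vs 95% | 19% | 15% |
| 79% vs 90% | 40% | 32% |
| 85% vs 95% | 49% | 39% |
| 80% vs 95% | 76% | 60% |
| 70% vs 90% | 82% | 66% |

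By the normal approximation, a correlation of 0.5 between the endpoints raises joint power by about 2 to 6 points.

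**4. If the significance level is split equally.** At two-sided 2.5%, power for dose maintenance at 64 per group falls to 69% (pooled normal) or 70% (exact). Restoring 80% needs 81 per group by the pooled formula, or 81 / 0.9 = 90 with 10% dropout, which is 180 in total.

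**5. Fixed sequence, dose maintenance first.** The first test keeps the full two-sided 5%. The 64 per group and the power of about 79% are unchanged, and the family-wise error over both endpoints stays at 5%.

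**The case against.** This is a condensed journal article. A testing order or alpha split is commonly placed in the full protocol or SAP, and neither is shown. Nothing printed says that one endpoint alone makes the trial positive. This stands, and the fix is worded accordingly. It does not remove the mismatch, because the article does print two primary endpoints, tests both, and sizes one.

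A reader might infer that the trial carries a false-positive risk of about 10%. The documents do not support that as a flat statement. The 9.75% needs an assumed 5% level, independent tests, and a rule that either win counts. Both endpoints are observed in the same patients over the same 16 weeks, so some correlation is plausible. The figure also counts false results in both directions. The risk of wrongly crediting HAD-B1 is at most about 4.9%.

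A reader might equally infer that power is very low if both endpoints are needed. That cannot be derived either. The Introduction calls disease control rates under afatinib high, but as general background, with no figure, no time point and no assumption for this trial's control arm. Gains of 15 to 20 points in DCR would give joint power of 60% to 66%.

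Finally, a fixed sequence is not the only valid remedy. An alpha split, or a properly sized requirement that both endpoints succeed, would also be sound. The choice belongs to the sponsor, provided section 2.9 then matches it.

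**Conclusion.** The point holds. The article names two primary endpoints, tests both, gives no success rule, and derives its sample size from dose maintenance alone.

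Under an either-endpoint rule, the family-wise error lies between 7.0% and 9.75% for correlations from 0.9 down to 0. That is above 5% throughout the range, and the risk of falsely favouring HAD-B1 is about 1.4 to 2 times that of a single test (3.5/2.5 to 4.9/2.5). Under a both-endpoints rule, power is unknown but cannot exceed about 79%. It is probably low if control DCR is high, though the documents do not establish how low.

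The sizing of dose maintenance itself reproduces and is not in question. These conclusions rest on the assumed two-sided 5% level and, for joint power, on assumed DCR rates and independence. An unseen SAP could already contain the missing rule.

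**What to change.** Unless the full protocol or SAP already fixes a rule, add one to sections 2.6 and 2.10.1 before outcome data are compared:

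- Starting-dose maintenance, the endpoint the trial was sized for, is tested first at two-sided 5%, and success is declared on it.
- DCR is tested at two-sided 5% only if the first test is significant. Otherwise it is reported as an estimate with a 95% confidence interval.
- Section 2.9 states that the 64 per group covers dose maintenance only.

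This costs about a paragraph across the three sections and no extra patients. The downside is that DCR alone could no longer make the trial positive.

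If the sponsor prefers to require both endpoints or to split the significance level, section 2.9 must restate the power that 64 per group gives under that rule. With an equal split, that is about 69% to 70% for dose maintenance. Under either alternative, section 2.9 also needs explicit DCR assumptions.
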